## Abstract

Background: The coronavirus disease 2019 (COVID-19) pandemic is currently ongoing, and there have been significant efforts in the development of COVID-19 vaccines. However, the neutralizing antibody titers in vaccinated individuals are reported to progressively decrease over time. Japanese pharmaceutical companies have published the results of Phase I and II studies on the safety and efficacy of different vaccines. Final clinical trials will be conducted with the aim of practical application by March 2023. To effectively utilize vaccines developed by Japanese companies, the efficacy and safety of a booster dose (i.e., third vaccination) must be evaluated among individuals who have received three doses of different vaccines. Methods: This protocol describes a study that aims to examine the effect of a booster dose of “KD-414”, a novel Japanese inactivated vaccine, on antibody titers among participants involved in a previous study. Volunteers in this protocol will be recruited from participants in the previous study and immunized with KD-414 after obtaining consent. The antibody titers, before and after immunization with KD-414, among participants who previously received two doses of the BNT162b2 mRNA vaccine, will be comparatively analyzed. Discussion: The reactogenicity and immunogenicity of seven different COVID-19 vaccines including an inactivated vaccine as a third dose after two doses of ChAdOx1 nCov-19 or BNT162b2, has been tested previously, and found to be superior to control (quadrivalent meningococcal conjugate vaccine) regardless of which vaccine had been received during the initial course. This suggests that many types of third booster doses are efficacious. It is anticipated that this study will provide evidence of the safety and immunogenicity of KD-414 as a booster vaccine, which will have profound public health implications.

## 1. Background

The coronavirus disease 2019 (COVID-19) vaccine developed by Pfizer-BioNTech, BNT162b2, was approved for emergency use on 14 February 2021 by the Japanese Ministry of Health, Labor and Welfare. Japan’s vaccination program for healthcare workers was started on 17 February 2021. The efficacy of the vaccine is reported to be >90% among individuals who have received two doses of the vaccine [1]. However, the neutralizing antibody titers in vaccinated individuals are reported to progressively decrease over time [2]. The administration of a third booster dose enhanced the neutralizing antibody titers. Based on these findings, the Centers for Disease Control and Prevention (CDC) Advisory Committee of the United States of America recommend a third booster dose for the elderly population (aged ≥ 65 years) and patients with comorbidities who are at high risk of severe COVID-19. The US Food and Drug Administration provided emergency use authorization for booster doses to various individuals, including those involved in high-risk occupations. The Japanese Health, Labor, and Welfare Council also acknowledged the need for booster doses. However, no novel COVID-19 vaccine was approved for booster doses until September 2021 and vaccination eligibility for specific booster doses is to be discussed on an ongoing basis.

Japanese pharmaceutical companies have published the results of Phase I and II studies on the safety and efficacy of different vaccines. Final clinical trials will be conducted with the aim of practical application by March 2023. To effectively utilize vaccines developed by Japanese companies, the efficacy and safety of booster doses must be evaluated among individuals who have received two doses of the BNT162b2 mRNA vaccine. It is important to evaluate the effect of combined vaccination, for which primary immunization was examined in detail, at this time, because the opportunity for evaluation in such a setting will be lost when additional immunization becomes widespread. Hence, it will be important to evaluate the effect of combined vaccination, for which primary immunization was examined in detail, at this time.

In March 2021, at public expense, the National Center for Global Health and Medicine (NCGM) conducted an observational study of 100 healthcare volunteers from NCGM staff vaccinated with the BNT162b2 mRNA vaccine (Pfizer-BioNTech). The antibody titers were monitored for nine months (*A survey of vaccine-induced COVID-19 antibody titer to verify temporal change*; NCGM Ethical Review Board Approval Number: NCGM-A-004175-04). An in-depth evaluation of the primary immunization revealed that the highest antibody titers were observed on day 7 post-second dose (day 28 post-first dose), which gradually declined thereafter [3,4].

A previous study has shown that a third dose with CoronaVac, an inactivated vaccine, given eight months after a second dose with CoronaVac, significantly increased neutralizing antibody concentrations against SARS-CoV-2 in healthy adults aged 18 years and older [5]. Another study investigated the reactogenicity and immunogenicity of seven different COVID-19 vaccines, including inactivated vaccine (VLA2001), as a third dose after two doses of ChAdOx1 nCov-19 or BNT162b2, showing that the immunogenicity of homologous or heterologous third dose booster vaccination with all tested vaccines was superior to control (quadrivalent meningococcal conjugate vaccine) regardless of which vaccine had been received during the initial course [6]. This suggests that many types of third booster dose are efficacious and supports the potential use of a booster dose of “KD-414”, a novel Japanese inactivated vaccine.

KD-414 is an inactivated vaccine against SARS-CoV-2 being developed by KM-Biologics Co., Ltd. (Kumamoto, Japan). It is an inactivated whole-particle vaccine containing aluminum hydroxide added as an immune aid after growth of SARS-CoV-2 on Vero cells from African green monkey kidney and purification and inactivation of the virus. Currently, Phase I/II clinical trials have been completed in Japan and have shown efficacy of KD-414 in adults and the elderly, and that adverse reactions are comparable to general inactivated vaccines with fewer adverse reactions than for mRNA vaccines. It is thought that KD-414 could provide a new option for those who have difficulty with existing vaccinations or who require higher levels of safety.

In a Phase 1/2 study conducted in JAPAN, only one convalescent fever (39 °C or higher) occurred in 29 subjects with severe adverse reaction after administration of KD-414 containing 10 μg of inactivated coronavirus (SARS-CoV-2). The neutralizing antibody GMT at 28 days after the second vaccination was 12.1 (IU equivalent 44.9–63.4 IU/mL) for adults (aged 20–64 years) and 7.3 (IU equivalent: 27.1–38.3 IU/mL) for the elderly (aged 65 years or older). It approximated an estimated neutralizing antibody titer of 54 IU/mL (95% CI 30–96 IU/mL) required to control the onset of disease [7] In addition, the value was higher than the neutralizing antibody titer for which a 70% efficacy rate of other vaccines could be expected [8].

This protocol describes a study that aims to examine the effect of a booster dose with KD-414 on the antibody titers among participants involved in the previous study [1,2]. Consenting volunteers will be immunized with KD-414. The antibody titers, before and after immunization with KD-414, among participants who had previously received two doses of the BNT162b2 mRNA vaccine will be comparatively analyzed. This trial was registered with the Japan Registry of Clinical Trials (Clinical Trial Plan Number: iRCTs031210388; https://jrct.niph.go.jp/latest-detail/jRCTs031210388; first registration date: 22 October 2021).

## 2. Methods

**Information on drugs used in clinical research (test/comparator products)**

**Name of the drug (generic and brand name)**

(1)Test vaccine: KD-414(2)Dosage form: Intramuscular injection(3)Properties: Exhibits uniform white turbidity upon shaking(4)Storage conditions: Maintained at 2–8 °C under light shielding(5)Composition: Each vial comprises 0.7 mL of KD-414. Each 0.5 mL of KD-414 contains 10 μg of inactivated coronavirus (SARS-CoV-2) as protein content and aluminum hydroxide as adjuvant.

**Dosage administration route and**
**volume**

Intramuscular administration with 0.5 mL/inoculation.

**Target population (age group, sex, and disease history)**

Individuals who have already received two doses of the BNT162b2 mRNA vaccine in the previous study (“*Study on the changes in antibody titers by vaccination with a novel coronavirus vaccine*”) will be enrolled in this study.

**Inclusion criteria**

(1)Individuals who have received two doses of BNT162b2 mRNA vaccine and have completed the measurement of antibody titer on Day 29 (Day 7 after the second dose) in the previous study [3,4].(2)Individuals who provide written informed consent, comply with the instructions during the study period, undergo medical examination specified in the study protocol, and can report symptoms.

**Exclusion criteria**

(1)Individuals who received three doses of the BNT162b2 mRNA vaccine at the time of obtaining informed consent.(2)Pregnant women, women who are potentially pregnant, women who wish to become pregnant before completing the post-test, and breastfeeding women.(3)Individuals with fibrodysplasia ossificans progressiva.(4)Individuals with underlying diseases, such as serious cardiovascular disease, kidney disease, liver disease, blood disease, developmental disorders, respiratory diseases, and diabetes mellitus.(5)Individuals with convulsion in the past.(6)Individuals with a previous diagnosis of immunodeficiency and those with relatives with congenital immunodeficiency.(7)Individuals who may be allergic to the ingredients of KD-414.(8)Individuals who have participated in another clinical trial within the past four months (120 days) from the date of proposed vaccination with KD-414 and who have received other test substances (excluding placebo), or who are scheduled to participate in another clinical trial during the study period.(9)Individuals who have received blood transfusions or gamma globulin products within the past three months (90 days) or have received high-dose gamma globulin products (200 or more mg/kg bodyweight) within the past six months (180 days) from the date of proposed vaccination with KD-414.(10)Patients who have received radiotherapy, immunosuppressive drugs (topical drugs are available), immunosuppressive therapy, antirheumatic drugs, adrenocorticotropic hormones, or corticosteroids that affect immune function within six months (180 days) after the date of vaccination (if the total daily dose of prednisolone was ≥2 mg/kg bodyweight and the treatment duration was ≥14 days, topical drugs may be used).(11)Individuals immunized with the live vaccine within one month or inactivated vaccine within one week.(12)Individuals with a history of breakthrough infection who wish to be immunized with KD-414.(13)Individuals judged by the investigator (or sub-investigator) to be ineligible for the study.

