**Individuals requiring caution about vaccination**

Patients who exhibit the pathological conditions listed below will be carefully monitored through medical examination, and their participation in the study will be considered. The patients will be informed about the aims and endpoints of the study, as well as adverse reactions. Informed consent will be obtained considering their health status and constitution before vaccination.

(1)Individuals with underlying diseases, such as cardiovascular disease, kidney disease, liver disease, hematological disease, developmental disorder, respiratory disease, and diabetes mellitus.(2)Individuals who have experienced fever within two days of vaccination or who have had suspected allergy symptoms, such as a generalized rash (not applicable if it is confirmed that the causative ingredient is not included in KD-414)(3)Individuals with convulsions in the past.(4)Individuals who may be allergic to any of the ingredients of KD-414 (thimerosal).

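### Past convulsions and possible ingredient allergy are both outright exclusions and caution conditions, and exclusion (10) and discontinuation criterion (2) are wrong as written

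*Protocol article*

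**What the plan says.** All of this is in section 2 (Methods) of the protocol article.

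- **Convulsions.** Exclusion criterion (5) is "Individuals with convulsion in the past". Under Individuals requiring caution about vaccination, item (3) is "Individuals with convulsions in the past".
- **Allergy.** Exclusion criterion (7) is "Individuals who may be allergic to the ingredients of KD-414". Caution item (4) is "Individuals who may be allergic to any of the ingredients of KD-414 (thimerosal", with the bracket closed after that word.
- **Effect of the caution list.** Its opening sentence says that people with the listed conditions will be "carefully monitored through medical examination, and their participation in the study will be considered".
- **Immunosuppression.** Exclusion criterion (10) covers radiotherapy, several classes of immunosuppressive treatment and "corticosteroids that affect immune function within six months (180 days) after the date of vaccination". A bracket then says that, given a prednisolone total of at least 2 mg/kg bodyweight per day for at least 14 days, topical drugs may be used.
- **Discontinuation.** Item (2) of Criteria for discontinuation ends participation when an exclusion criterion is not satisfied.

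**The concern.** Eligibility rules should give one answer for each volunteer. Here a person with a past convulsion, or a possible allergy to an ingredient, is refused by one list and open to consideration under the next, and no rule says which list takes precedence.

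Exclusion (10) and discontinuation criterion (2) have a different fault: each says something its authors cannot have meant. Taken literally, (10) does not exclude someone immunosuppressed before the dose, and discontinuation (2) would remove the whole eligible study population.

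What is at stake is the safety screen. The Ethical considerations section describes KD-414 as unapproved, with too little vaccination experience to rule out unknown adverse events. Convulsion history, ingredient allergy and immunosuppression are central to that screen.

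**Working it through.** The plan gives no figure to reproduce here. The check is a comparison of the texts and a count.

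**1. Do the two lists separate the same people?**

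| Condition | Exclusion criteria | Caution list | Separating word |
|---|---|---|---|
| Underlying disease | (4) "Individuals with underlying diseases, such as serious cardiovascular disease" and others | (1) "Individuals with underlying diseases, such as cardiovascular disease" and others | *serious*, in (4) only |
| Past convulsion | (5), no qualifier | (3), no qualifier | none |
| Possible ingredient allergy | (7), no qualifier | (4), names thimerosal | none that works |

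The first row shows how the lists can coexist: serious disease excludes, milder disease calls for caution. Nothing similar appears in the second row. In the third row the mention of thimerosal does not separate the groups. Item (4) speaks of any of the ingredients and gives thimerosal as one of them, so a person possibly allergic to it also meets exclusion (7), which has no exception. Caution item (2), on fever and suspected allergy symptoms around vaccination, has no identical exclusion and is not counted.

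**2. Exclusion (10), time window.** Criteria (8) and (9) look back from the proposed vaccination date: 120 days in (8), 90 and 180 days in (9). Criterion (10) alone says 180 days *after* vaccination. Eligibility is confirmed at Visit 1, before inoculation, so treatment after the dose cannot be known then. Observation ends at day 40, so a 180-day forward window could not be assessed within follow-up either.

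**3. Exclusion (10), bracket.** As worded, a high prednisolone dose is the condition for allowing topical drugs. It should define the corticosteroid exposure that excludes. A screener cannot tell from the text whether a lower dose or shorter course excludes a volunteer. Topical use has already been exempted earlier in the same criterion, next to immunosuppressive drugs.

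**4. Discontinuation (2).** An eligible participant is someone for whom no exclusion criterion is satisfied. The criterion as written is therefore true of all of them.

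**5. Count.**

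- Exclusions (5), (7) and (10): 3 of 13.
- Caution items (3) and (4): 2 of 4.
- Discontinuation criterion (2): 1 of 5.

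The document does not say how many volunteers would be affected.

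**The case against.** The strongest reply is that nothing unsafe follows. Exclusions ordinarily prevail over a caution list, and the caution list does not claim to override them. The investigator can also refuse a volunteer under exclusion (13), defer vaccination under item (3) of the deferral criteria, and settle doubtful cases under Handling of cases. All of this stands, and it is why the point is minor. But if exclusions prevail, caution items (3) and (4) can never apply, yet they still tell staff that such people may be considered. One of the two lists needs editing on either reading.

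On allergy, one can argue that the specific rule displaces the general one, so that possible thimerosal allergy is considered case by case and other ingredient allergies exclude. That would work if (7) carried an exception or (4) were limited to thimerosal. Neither is so.

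On exclusion (10), the criterion opens in the past tense and its neighbours look back, so *after* reads as a slip, not a coherent forward-looking rule. That is fair, and so is the remark that no investigator would discontinue every eligible subject. The intent is recoverable in both cases, and translation may explain the wording. These are nevertheless the operative rules as published.

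Two smaller points also stand. Criteria (8) and (9) support the direction of the corrected window, but only one of the windows in (9) supports its length. Discontinuation (2) might have been meant to say that an *inclusion* criterion is not satisfied, and the document does not decide between the two readings.

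**Conclusion.** The concern holds and is minor. The convulsion duplication is a plain contradiction. The allergy pair is also contradictory, because the thimerosal bracket does not create a separate group. Exclusion (10) has the wrong time direction and a misplaced threshold, and discontinuation criterion (2) is inverted.

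Six rules are affected in all (3 + 2 + 1). No effect on the primary GMT comparison, sample size or power is claimed, and no count of affected volunteers can be derived. The minor rating assumes that sites would let exclusions prevail and would read (10) and discontinuation (2) as evidently intended.

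**What to change.** Make five wording edits:

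1. Delete caution item (3).
2. Delete caution item (4). Exclusions (5) and (7) stay. The alternative to edits 1 and 2 is for the investigator and the review board to define a milder subset for the caution list, as *serious* does for underlying disease. Caution item (2) is unchanged.
3. In exclusion (10), set the window to the 180 days *before* the proposed vaccination date.
4. In exclusion (10), use the prednisolone threshold to define the excluded corticosteroid exposure, and state the topical exemption once. With edits 3 and 4 it could read: *Treatment in the 180 days before the planned KD-414 dose with radiotherapy, immunosuppressive drugs or other immunosuppressive therapy, antirheumatic drugs, adrenocorticotropic hormone, or corticosteroids at a level affecting immunity (daily prednisolone total ≥2 mg/kg for ≥14 days). Topical preparations are permitted.*
5. Reword discontinuation criterion (2) as *An exclusion criterion is found to be met*. If failure of an inclusion criterion was also intended, add it explicitly.

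The cost is a text amendment, with no change to the design, sample size or analysis.

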**Individuals requiring caution about vaccination**

Patients who exhibit the pathological conditions listed below will be carefully monitored through medical examination, and their participation in the study will be considered. The patients will be informed about the aims and endpoints of the study, as well as adverse reactions. Informed consent will be obtained considering their health status and constitution before vaccination.

(1)Individuals with underlying diseases, such as cardiovascular disease, kidney disease, liver disease, hematological disease, developmental disorder, respiratory disease, and diabetes mellitus.(2)Individuals who have experienced fever within two days of vaccination or who have had suspected allergy symptoms, such as a generalized rash (not applicable if it is confirmed that the causative ingredient is not included in KD-414)(3)Individuals with convulsions in the past.(4)Individuals who may be allergic to any of the ingredients of KD-414 (thimerosal).

**Criteria for postponement of vaccination and discontinuation of KD-414**

**Criteria for deferring vaccination of test drugs**

Vaccination will be postponed for study subjects who meet any of the following criteria on the scheduled date of vaccination with KD-414. However, if the vaccination deferral criteria are no longer met, vaccination may be performed.

(1)Individuals with fever (above 37.5 °C).(2)Individuals suffering from serious acute illness.(3)The investigator or sub-investigator judges the vaccination with KD-414 to be inappropriate.

**Criteria for discontinuation**

The study participation will be discontinued under the following conditions:(1)Subjects request withdrawal of consent to participate in the study.(2)An exclusion criterion is not satisfied.(3)Compliance with the study protocol is not possible.(4)The study is discontinued.(5)The investigator or sub-investigator judged the continuation of the study to be difficult.

**Content of clinical research**

Type of clinical trial

Open-label, single-arm study.

**Randomization and blinding**

Not applicable.

**Use of pharmaceuticals and medical devices for study subjects**

**Details of treatment period and observation period (including follow-up)**

The schedule of KD-414 inoculation has been approved by the Clinical Research Review Board. The treatment period is one day, followed by a 40-day observation period.

**Specific methods (including schedules)**

The study will be conducted according to the schedules shown in Table 1, Table 2 and Table 3 and the recruitment process is shown in Figure 1.

If a third dose of BNT162b2 mRNA is received in the future at public expense, the immunogenicity-related parameters and adverse events will be recorded on days 0, 7, and 40 post-vaccination.

**Visit 1 (Inclusion of study subjects and KD-414 vaccination/registration)**

(1)The investigator or sub-investigator will explain the test and obtain consent in advance. This is described in further detail in the section titled “Method of obtaining consent for clinical research subjects”.(2)The investigator or sub-investigator will confirm the background and eligibility of the study subjects and prepare a registration form.

(hereafter, only in the KD-414 group)

(1)The investigator or sub-investigator will collect the blood for immunogenicity evaluation.(2)The investigator or sub-investigator will conduct physical examination and body temperature measurement for study subjects and inoculate them with KD-414 if the inoculation is judged to be feasible.(3)Follow-up observation will be performed for approximately 15–30 min after the inoculation of KD-414. In case of an adverse event, the investigator or sub-investigator will take appropriate measures.(4)The symptoms should alleviate or stabilize if it is judged necessary to continue to confirm the safety due to the occurrence of adverse events.(5)Study subjects vaccinated with KD-414 will be requested to complete a health diary

